### Subjects

Two thousand two hundred forty nine children aged 8 to 10 years (4^th^ and 5^th^ grade of elementary school) were recruited from 4 Catalan cities (Terrassa, Sant Boi de Llobregat, Molins de Rei, and Gavà) from September to November 2012. The Thao-Child Health Program was implemented in Terrassa y Sant Boi de Llobregat whereas Molins de Rei and Gavà serve as control cities.

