### Sample size calculation

The sample size calculation is based on data on 1 year changes in BMI of children from 14 towns where the THAO intervention program has been implemented. A decrease in BMI of 0.55 kg/m^2^ was observed. Therefore, we considered reasonable to assume a difference in BMI of 0,6 kg/m^2^ between control and intervention group. 1070 participants in each group are necessary to detect a difference in BMI of 0.6 kg/m^2^ or higher assuming a 0,05 alpha risk and 0,2 beta risk in a bilateral contrast. A BMI standard deviation of 4.43 kg/m^2^ was assumed and 20% of missing during follow up was estimated.

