### Statistic

Data clean-up will be performed to minimize errors. Linear multivariate mixed models will be fit to analyze differences in changes in quantitative variables between groups. Pre-post changes will be considered as the response variable, and participants’ (age, gender, etc.) and municipalities’ characteristics (group membership) will be included as fixed effects explanatory variables. Additionally, to account for the hierarchical structure of the data, municipalities (Terrassa, Sant Boi de Llobregat, Molins de Rei, and Gavà) will be added to the model as random effects factors.

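### The programme effect rests on four towns (2 between-town df) and the article fixes no matching reference distribution; a large-sample test would reject a true null in about 13% to 18% of trials at assumed town ICCs of 0.005 to 0.02

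*Protocol article*

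**What the plan says.** The Subjects section assigns whole towns: "The Thao-Child Health Program was implemented in Terrassa y Sant Boi de Llobregat whereas Molins de Rei and Gavà serve as control cities". The Discussion confirms two intervention and two control towns.

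The Statistic section takes pre-post change as the response for all quantitative variables. Group membership is a fixed effect, and "municipalities (Terrassa, Sant Boi de Llobregat, Molins de Rei, and Gavà) will be added to the model as random effects factors". The stated purpose is to respect the hierarchy of the data. The section names no estimator (REML or ML), no reference distribution and no method for denominator degrees of freedom.

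The Sample size calculation uses "0,05 alpha risk and 0,2 beta risk in a bilateral contrast" to detect 0.6 kg/m². It adds that "A BMI standard deviation of 4.43 kg/m^2^ was assumed" and "20% of missing during follow up was estimated", and concludes that "1070 participants in each group are necessary". It contains no ICC or other clustering term.

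**The concern.** Group is constant within town, so the error for the programme effect is the variation between towns within an arm. That variation is estimated from 2 df, however many children are measured. A town variance estimated this poorly causes two problems:

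- It is often estimated as zero. The model then tests the programme as if the children were independent.
- When it is not zero, a large-sample reference uses 1.96 where 2 df call for 4.30.

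In either case the interval for the group effect can be too narrow. The same model serves every quantitative outcome, so the choice of reference affects the whole efficacy assessment.

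**Working it through.** **Inputs from the article.** Four towns, two per arm. Two-sided alpha 0.05, power 0.80, difference 0.6 kg/m², SD 4.43 kg/m², 20% missing, 1070 per group, 2249 children recruited.

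**Assumptions.** Town ICC of the change from 0 to 0.10, as none is stated. Equal town sizes, no covariates, and 4.43 used as the SD of change. Type I error does not depend on the SD.

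**1. The plan's own figure.** n = 2(1.96 + 0.8416)² × 4.43² / 0.6² = 855.7, so 856 evaluable per group. Then 856 / 0.8 = 1070, an exact match. The calculation therefore treats children as independent.

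**2. Degrees of freedom.** 4 towns - 2 group means = 2. The two-sided 5% critical value of t on 2 df is 4.303. For t on 2 df, P(|t| > c) = 1 - c/√(2 + c²). With c = 1.96 this is 1 - 1.96/√5.8416 = 18.9%, the limit for REML with 1.96 as the ICC grows.

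**3. How often town variance is estimated as zero.** With m children per town, λ = 1 + m·ICC/(1 - ICC), and the probability is about 1 - exp(-1/λ). With m = 856/2 = 428 and ICC 0.005, λ = 3.15 and the probability is 27%.

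**4. Rejection of a true null.** Simulation with 1,000,000 runs per setting. Each cell gives 428 / 562 children per town (562 = 2249/4).

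| Town ICC | REML, 1.96 (%) | Zero-bounded REML, 4.30 (%) | Town-level t, 2 df (%) | Variance estimated as zero (%) |
|---|---|---|---|---|
| 0 | 3.7 / 3.7 | 0.0 / 0.0 | 5.0 / 5.0 | 63 / 63 |
| 0.0005 | 5.2 / 5.8 | 0.0 / 0.0 | 5.0 / 5.0 | 56 / 54 |
| 0.001 | 6.6 / 7.4 | 0.0 / 0.0 | 5.0 / 5.0 | 50 / 47 |
| 0.005 | 13.0 / 14.1 | 0.5 / 0.8 | 5.0 / 5.0 | 27 / 23 |
| 0.01 | 15.7 / 16.5 | 1.5 / 2.0 | 5.0 / 5.0 | 17 / 14 |
| 0.02 | 17.4 / 17.9 | 2.8 / 3.4 | 4.9 / 5.0 | 10 / 8 |
| 0.10 | 18.8 / 18.8 | 4.7 / 4.8 | 5.0 / 5.0 | 2 / 2 |

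Three further results:

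- **Satterthwaite.** With df reverting to large df at zero variance (450 children per town), the rates are 7.5%, 7.2% and 6.3% at ICC 0.005, 0.01 and 0.02.
- **ML instead of REML, with 1.96.** The rates are 23.8% / 25.3% at ICC 0.01, with a limit of 30.0%.
- **School clustering.** An added school ICC of 0.02 (10 schools per town assumed, 450 children per town, REML with 1.96) gives 14.5%, 16.4% and 17.7% at town ICC 0.005, 0.01 and 0.02.

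**5. Power of the valid test.** The variance of a town mean is v = SD²[ICC + (1 - ICC)/m]. The difference between two arm means, each the average of two towns, also has variance v.

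- ICC 0: v = 19.625/428 = 0.0459, SE 0.214, 0.6/SE = 2.80. Power on 2 df is 35%.
- ICC 0.01: v = 19.625 × (0.01 + 0.99/428) = 0.2416, SE 0.492, 0.6/SE = 1.22. Power on 2 df is 12%.

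The same test has 27% power at ICC 0.001, 16% at 0.005 and 9% at 0.02.

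**The case against.** The strongest reply is that the article commits to no z or residual-df test. The df method is commonly left to an analysis plan, and that plan is not shown. A mixed model with nested or containment df would use 2 df, would match the Statistic section word for word, and would not inflate the error. This stands. A reader might infer that the plan as written yields intervals that are too narrow and false-positive claims for every outcome. The document does not support that. It specifies no such test, and inflation depends on each outcome's town ICC, which is not given.

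A second reply is that inflation disappears when towns barely differ. This also stands: with REML and 1.96 the rate is 3.7% at ICC 0 and 5.2% to 5.8% at 0.0005.

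A reader might also join the results into one range from about 7% to 18%. At ICCs of 0.005 to 0.02 those ends belong to different tests: the low end is Satterthwaite and the high end is a large-sample reference.

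Nor is putting town in the model the mistake. With no town effect, a z test rejects in 39.5% of null runs at ICC 0.01 (428 per town).

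What remains is that a four-level random effect, tested in either of two common ways, exceeds 5% at ICCs of 0.005 to 0.02. The containment route avoids this only by becoming strongly conservative under an ordinary zero-bounded REML fit. Its power for 0.6 kg/m² is 4.7% at ICC 0 and 7.4% at 0.01, against 35% and 12% for the town-level t test.

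**Conclusion.** The point holds in conditional form. The 2 between-town df follow from the article's own design and do not depend on any assumption. The size of the inflation depends on the reference used and on an ICC that the documents do not give. At town ICCs of 0.005 to 0.02 it is about 13% to 18% for REML with a Wald or large-df reference, and about 6% to 7.5% for Satterthwaite with reversion. ML with 1.96 would be worse. The figures assume equal towns.

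The planned 80% power cannot be kept alongside a valid 2-df test under the article's own SD and difference, even at ICC 0. A smaller SD of change would raise the powers shown, but the documents give none.

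**What to change.** In the Statistic section, make the test of group membership a two-stage analysis:

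1. Adjust individual changes for child-level covariates and obtain the four town mean changes.
2. Compare the two arms by t on 2 df, with multiplier 4.30 for the interval.
3. Report the four town-specific mean changes beside the estimate.
4. Do not base the programme effect on Wald z or residual-df p-values.

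Further town-level covariates should stay out of this test, because each would take one of the 2 df. A zero-bounded REML fit with df set to 2 is not an adequate substitute: it rejects about 0% of true nulls at ICC 0 and 1.5% to 2.0% at 0.01. A permutation test over towns does not help either. There are only 6 ways to choose two towns of four, so the smallest two-sided p is 2/6 = 0.33.

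No new data are needed. The cost is precision. At ICC 0 the half-width for BMI change goes from about 1.96 × 0.214 = 0.42 to 4.30 × 0.214 = 0.92 kg/m², and at ICC 0.01 it is about 4.30 × 0.492 = 2.1 kg/m². The Sample size calculation should say that its 80% treats children as independent, and should restate power for the 2-df test over a declared range of town ICCs.

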### Ethical issues

Parent consent was requested for each children and were performed parent meetings as requested by the schools. At any time the children or their family can leave the study and the data is automatically deleted.

The collection of anthropometric variables was performed in strict privacy conditions and gender dependent.

The study protocol was approved by the ethical committee of IMAS – Parc de Salut Mar, Barcelona, Spain.

## Discussion

The obesity epidemic is one of the biggest current challenges for health policy. The economic burden of obesity is estimated to be at around 10 percent of total health care costs [20]. Obesity prevalence has reached epidemic proportions and is associated with numerous cardiovascular risk factors in adults and children [2]. About 60% of the Spanish adult population are overweight or obese [21]. But most alarming is the high proportion of Spanish children and adolescents with excessive body weight. Currently four out of ten Spanish children between the ages of 8 and 17 suffer from excessive body weight [6]. This reflects one of the highest prevalence rates of childhood obesity among European countries [22]. This is of particular concern given the high probability that childhood obesity tends to continue into adulthood.

Therefore, intervention programs to prevent childhood obesity are needed. This in turn will improve the health status of children and reduce the economic burden of obesity. Several CBI programs that include families and key local community members have been developed mainly in the United States [23]. Some [24-27] but not all [28-32] of these CBI programs showed a favorable impact on lifestyle and anthropometric surrogate measures of adiposity.

A significant reduction in BMI z-scores has been reported by four CBI programs [24-27]. Additionally, de Silva-Sanigorski and colleagues showed an improvement in diet quality [26]. Improved physical fitness and an increase in physical activity were reported by Chomitz et al. [25] and Sallis et al. [24], respectively.

There is little data about the effect of CBI programs in European countries [28,29]. Therefore, it is paramount to develop and implement CBI programs tailored for country specific conditions in Europe. The POIBC study aims to determine the efficacy of the THAO-Child Health Program, a multisetting and multistrategy CBI program based on EPODE methodology [33]. The THAO-Child Health Program has been implemented in 75 towns in Spain since 2007. A basic characteristic of this program is the coordination by local authorities (municipalities) and the involvement of key sectors, such as schools, kindergarten, markets, sports and leisure time associations, health care providers and other local institutions relevant for child health. The TCHP includes health promotion materials and actions, permanent training of local coordinators and the development of an assessment and communication plan. This study represents an advance with respect to previously reported interventions in childhood obesity because the TCHP represents a sustainable intervention for municipalities and offers the possibility of maintain existing actions. Furthermore, the actions are carried out under the same communication model, and cartoon characters called “Thaoines” facilitate the health education of children. The TCHP is based on the I-Change Model defined by de Vries (last updated I-Change Model 2.0, 2008 [34]). This model is an amplification of the ASE model [Attitude – Social influence – self Efficacy Model [35]). The basic concept of the I-Change Model is an integration of ideas from Ajzen’s Theory of Planned Behaviour] [36], Bandura’s Social Cognitive Theory [37], Prochaska’s Transtheoretical Model [38], the Health Belief Model [39] and goal setting theories [40].

The POIBC study includes 2 intervention and 2 control towns and monitorate anthropometric variables and obesity related behaviour. Furthermore, parental socioeconomic status and lifestyle are recorded. An innovative aspect of the POIC study is the implementation of an on-line questionnaires to record lifestyle variables in children. Compared with the paper versions, the on-line software allows the children to answer in a more dynamic way. This, in turn, may help reduce mistakes in the response process.

A limitation of the POIBC study is its non-representative design. However, intervention and control towns have similar sociodemographic and socioeconomic characteristics, and are located in the same geographical area.

The POIBC study assesses changes in intervention and control towns during two complete academic years. This study will provide evidence about the efficacy of THAO-Child Health Program in Spain to confront the childhood obesity epidemic. Furthermore, it will give us a better understanding of the impact of this program on the development of obesity related behaviours.

## Abbreviations

CBI: Community based interventions programs; sDQS: Diet quality screener; DEBQ-C: Dutch eating behaviour questionnaire for children; EPODE: Ensemble Prévenons l'ObésitéDes Enfants; OECD: Organisation for Economic Co-operation and Development; PSQ: Pediatric sleep questionnaire; PAQ-C: Physical Activity Questionnaire for Children (PAQ-C); sMLTPA: Short version of the Minnesota leisure-time physical activity questionnaire; TCHP: THAO-Child health program.
